## Effectiveness Study

A schematic of the study design that illustrates the effectiveness investigation is depicted in Figure 2. For the last 6 months of each cluster's pre-I phase, eligible participants are invited to consent to monthly administration of a collection of PRO surveys administered through REDCap for one year following consent. One set of comprehensive PRO surveys will be administered at baseline and monthly thereafter, and an additional set of questionnaires will be included with these PRO surveys on a quarterly basis (see Section 2.0 for primary and secondary effectiveness PROs and timing). During post-I, EC becomes available using a 1:1 randomization scheme (EC:UC) to new, consenting patients, but not those in the consented group from the pre-I period who are continuing their care. Randomization will be stratified by cluster, cancer continuum (curative, non-curative, survivorship), gender and language preference. Participants who consent to randomization during post-I will receive the REDCap PRO surveys on the same schedule as those who consented during the pre-I phase. The monthly PRO data collected over one year of follow-up during the post-I embedded patient-randomized trial will be the primary data source for the effectiveness analysis. Additionally, we will compare the post-I EC and UC arms to patients enrolled during pre-I. Pre-I patients will have access to identical tools as UC patients, and the comparison of these arms will be critical for noting potential contamination in provider care subsequent to system-wide implementation strategies.

| Clinical Cluster | Implementation Phase | Y3                         |                            |                              |                              | Y4                                                    |                                                       |                                                       |                                                       | Y5                                                    |                                                       |                                                       |    | Y6 |    |    |    |

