### Effectiveness

Target enrollment in the patient-randomized trial comparing EC v. UC in the post-I phase is approximately 1000 patients. The target enrollment for the patient-randomized component of the trial was based on planned longitudinal modeling of monthly evaluations of 5 PROs for anxiety, depression, fatigue, physical functioning and pain interference. Assuming a compound symmetry covariance structure for the longitudinal measurements with within-subject correlations of 0.5 at all time points, a sample size of 360 is required to achieve 90% power to achieve statistical significance at a Bonferroni-corrected  $p < 0.01$  for an anticipated average difference of 0.3 SD across all time points for EC v. UC. An overall recruitment goal of  $n=1000$  was set to accommodate dropout of up to 64% of patients over time. A Bonferroni correction was used for a conservative estimate of required sample size; for statistical analyses the more powerful step-down Dunnett procedure will be used for p-value adjustment. It is also noted that the target sample size of  $n=1000$  also provides greater than 90% power for detecting a 0.3 SD difference in the FACT G-7 (evaluated at 5 time points) under similar covariance assumptions as the other PROs, as well as simple change-from-baseline differences in PROs from 0 to 12 months using linear models.

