## 9.0 STATISTICAL ANALYSES - EFFECTIVENESS

### 9.1 Primary Outcomes - Effectiveness

#### PROs

Using each of the separate PROMIS domain status scores (i.e., Anxiety, Depression, Fatigue, Pain Interference, and Physical Function) collected at baseline and at regular monthly intervals, primary analyses will use longitudinal models to estimate the time-averaged difference in PROs across groups. Primary effectiveness estimates will be based on post-I data with a comparison of longitudinal PROs for patients randomized to Post-I EC v. Post-I UC. Linear mixed models will be used for these analyses with a fixed effect for treatment arm (Post-I EC v. Post-I UC) as the primary predictor of interest and fixed effects for model adjustments for cluster, cancer continuum, gender, language preference, baseline PRO value and time of enrollment (categorical variable for quarter enrolled). Individual-level random effects with an autoregressive covariance structure will be included in the mixed models to account for dependence of within-individual PRO measurements over time. Multiple comparisons adjustment for the five primary tests of hypothesis will be performed using the step-down Dunnett procedure. For reporting purposes, confidence intervals for treatment effects for the five primary outcomes will be reported with lower and upper bounds simultaneously estimated to correspond with Dunnett correction. Sensitivity of model estimates and statistical inference under unstructured and compound symmetry covariance structures will be explored. In addition to the overall time-averaged difference, we will also report estimated differences from baseline at specific monthly timepoints.

Secondary analyses will also examine changes from baseline to the 12-month follow-up time point as well as change from baseline to the other monthly follow-up time points using the directly observed differences from baseline at these timepoints. Linear regression will be used for these analyses with treatment arm (Post-I EC v. Post-I UC) as the primary predictor of interest and model adjustments for cluster, cancer continuum, gender, language preference, baseline PRO value and time of enrollment (categorical variable for quarter enrolled). These effect estimates will be compared to effect estimates at each time point calculated in the primary analysis model that uses all longitudinal measurements.

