Recognizing the possibility of contamination effects for the treatment arms during the post-I period, we will augment the primary analyses to include longitudinal PRO data from the Pre-I period. Linear mixed models will be used as described for the primary analyses but extending the primary predictor of interest to a multicategory variable (Post-I EC, Post-I UC, Pre-I). Adjustments for cluster, cancer continuum, gender, language preference, baseline PRO value and time of enrollment, and the individual-level random effects, will be included as described above. The Post-I UC cohort will be treated as the referent group to facilitate formal primary comparison with outcomes for the Post-I EC group, and to gauge comparability of outcomes for Post-I UC and Pre-I patients. This approach will also allow for a contrast test between Post-I EC and Pre-I. If longitudinal PROs for Post-I UC and Pre-I are not significantly different, and if the effectiveness estimate for Post-I EC v. Pre-I is similar to the primary Post-I EC v. Post-I UC comparison, this will suggest lack of contamination. If longitudinal PRO differences for Post-I UC v. Pre-I are significantly different and/or the effectiveness estimate for Post-I EC v. Pre-I is different from the primary Post-I EC v. Post-I UC comparison, this may suggest some level of treatment arm contamination during the Post-I phase. This latter scenario may also be indicative of system-level implementation effects and will need to be interpreted in the context of implementation analysis findings.

Multiple imputation using chained equations will be used for missing data under a range of scenarios from missing at random to informative missingness. Sensitivity of parameter estimates to these assumptions will be evaluated.

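### SAP 9.1 reads a non-significant Post-I UC v. Pre-I difference as suggesting no contamination, without a margin, although the cluster and enrolment-quarter adjustment raises that contrast's standard error about 1.5 to 2 times

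*Combined protocol and SAP*

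**What the plan says.** SAP 3.0 (Effectiveness Study) gives the Pre-I cohort the same tools as Post-I UC and says that "the comparison of these arms will be critical for noting potential contamination in provider care".

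SAP 9.1 (PROs) puts the check into one three-group mixed model with Post-I UC as referent. The absence reading needs two conditions. The first is a significance test: "If longitudinal PROs for Post-I UC and Pre-I are not significantly different". The second sets two point estimates against each other without a tolerance: "if the effectiveness estimate for Post-I EC v. Pre-I is similar to the primary Post-I EC v. Post-I UC comparison". Where both are met, the SAP's reading is that "this will suggest lack of contamination". If either fails, the SAP says there may be some contamination, or a system-level implementation effect to be read alongside the implementation findings.

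On covariates the same section says "Adjustments for cluster, cancer continuum, gender, language preference, baseline PRO value and time of enrollment, and the individual-level random effects, will be included". The primary analysis paragraph defines the time term: "time of enrollment (categorical variable for quarter enrolled").

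Neither document gives a margin, an alpha, a meaning for similarity or a power statement for this contrast. SAP 6.0 sizes only EC v. UC, for an "anticipated average difference of 0.3 SD across all time points for EC v. UC", with about 1000 randomised. It sets no target for consented Pre-I patients. Protocol 4.0 gives 6,336 Pre-I and about 3,168 per randomised arm.

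**The concern.** Failing to find a difference is evidence of no difference only when the contrast is precise enough to have shown one. Here precision is not stated, and the design works against it. EC and UC patients enrol side by side in the same clusters and quarters. Pre-I patients never share a cluster and quarter with UC patients. With both factors in the model, UC v. Pre-I rests on the limited overlap between clusters at different steps.

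The second condition looks like corroboration but is not. Within one model, (EC − Pre-I) − (EC − UC) = UC − Pre-I, so it re-reads the same estimate without its standard error.

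At stake is the reading of a small or null EC v. UC result. If UC patients picked up part of the benefit and the check is reported as reassuring, a diluted effect may be taken for an ineffective intervention.

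**Working it through.** **Inputs from the documents.** SAP 6.0: 0.3 SD average difference, compound symmetry with correlation 0.5, two-group total 360 for 90% power at p < 0.01, about 1000 enrolled, dropout up to 64%. SAP 3.0: seven clusters stepping quarterly, Pre-I recruitment in the last 6 months before transition, 1:1 allocation. Figure 2 reads as two quarters of randomised recruitment; protocol 4.0 assumes nine months, so three quarters were also run.

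**Assumed, because the documents are silent.** Pre-I size, two-sided alpha 0.05 for this contrast, 0.15 SD (half of 0.3) as the shift to detect, equal cluster sizes.

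**Step 1: reproduce the SAP's figure.** Variance of a 12-month mean = (1 + 11 × 0.5)/12 = 0.5417. Per arm, 2 × (2.576 + 1.282)² × 0.5417/0.3² = 179.1, so 180, or 360 in total. 360/(1 − 0.64) = 1000. Both match.

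**Step 2: cost of the adjustment.** Cluster k enrols Pre-I in quarters k and k+1, and UC and EC in k+2 and k+3. Weighted least squares on subject means gives these SE ratios for UC v. Pre-I, relative to no adjustment:

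| Adjustment and layout | SE ratio |
|---|---|
| Cluster only | 1.00 |
| Quarter only | 1.11 |
| Both, equal groups, two post-I quarters | 1.97 |
| Both, equal groups, three post-I quarters | 1.79 |
| Both, two post-I quarters, Pre-I twice the UC size | 1.96 |
| Both, two post-I quarters, Pre-I 6,336 v. UC 500 | 1.48 |

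The two factors together cause the inflation. For EC v. UC the ratio is 1.00 throughout.

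**Step 3: significance condition alone, one domain.** The planned baseline adjustment reduces the variance to 0.5417 − 0.5² = 0.2917. At 500 v. 500, the SE without cluster and quarter terms is √(2 × 0.2917/500) = 0.0342; with them, 0.0342 × 1.97 = 0.067. Miss probability for shift d = Φ(1.96 − d/SE) − Φ(−1.96 − d/SE).

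| Pre-I v. UC, baseline-adjusted | SE | 95% CI half-width | Miss at 0.15 SD |
|---|---|---|---|
| 500 v. 500 | 0.067 | 0.13 SD | 39% |
| 180 v. 180 (64% contribute nothing) | 0.112 | 0.22 SD | 73% |
| 6,336 v. 500 | 0.037 | 0.07 SD | 2% |
| 6,336 v. 3,168 | 0.023 | 0.05 SD | <1% |

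With the unadjusted SE of 0.0342, the first row's miss rate would be about 1%. Without baseline adjustment, which is not the planned model, the four rates are 63%, 83%, 16% and <1%. Simulation at 500 and 180 per group, baseline-adjusted, gave 40% and 75%.

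The size of the shift matters: at 500 v. 500, baseline-adjusted, the miss rate is 68% for 0.10 SD, 16% for 0.20 SD and under 1% for 0.30 SD.

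**Step 4: both conditions together.** If similar means within 0.10 SD (assumed), the estimate must also lie within ±0.10. For a true 0.15 SD shift, the pass probability is Φ((0.10 − 0.15)/SE) − Φ((−0.10 − 0.15)/SE): 23% at SE 0.067 and 31% at SE 0.112.

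**The case against.** The strongest objection is that Step 3 is not the SAP's rule. The rule needs both conditions, and the similarity condition can flag a large estimate that is not significant. This stands. The 39% to 73% covers one condition and is an upper bound for the whole rule; 23% to 31% is closer, but depends on an assumed meaning of similar.

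The 73% is also an extreme. SAP 7.1 keeps anyone with a baseline and one later measure, and a mixed model uses partial follow-up. If dropout rises linearly to 64% at month 12 (assumed), the miss rate at 500 v. 500 is 47% and the half-width 0.14 SD.

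The Pre-I size is assumed, and the only documented figure, 6,336, largely removes the problem at full retention. That holds if the figure still applies. It belongs to a protocol plan with 6,336 randomised, where the SAP now plans about 1000.

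Five domains are examined. If all five shift by 0.15 SD (inter-domain correlation 0.6 assumed), none is significant in 13% of trials at 500 per group and 45% at 180, baseline-adjusted.

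Finally, the SAP's wording is hedged, and the check does not alter the primary EC v. UC estimate. Both are true, but this remains the only prespecified reading of a comparison that the SAP calls critical.

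**Conclusion.** The point stands as a weakness of the stated rule. It turns a non-significant result, on a contrast whose SE the adjustment raises about 1.5 to 2.0 times, into a suggestion of absence, with no margin and an undefined second condition that is not independent evidence. At 500 v. 500 under the planned model, a non-significant result can coexist with contamination of half the planned effect. The miss rates rest on the assumed Pre-I size, alpha, shift and retention, and are small if Pre-I is in the thousands.

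A reader might infer that most contaminated trials would be declared clean. The documents do not support that: it ignores the second condition and the five domains, and needs a Pre-I size that the SAP does not state. Nor does the point touch the randomised EC v. UC comparison, whose precision the adjustment leaves unchanged.

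**What to change.** In SAP 9.1, replace the significance rule with an interval rule. Report UC − Pre-I with its 95% CI for each PROMIS domain, against a margin that the sponsor prespecifies, for example a stated fraction of the 0.3 SD design effect. Then conclude:

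- no material contamination, only if the CI lies inside the margin;
- contamination or implementation effect, if the CI excludes zero in the beneficial direction and is not inside the margin;
- inconclusive otherwise.

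Drop the similarity condition as separate evidence. State the Pre-I size and the expected precision of this contrast. Keep the cluster and quarter terms, which guard the comparison against calendar trends.

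This changes SAP wording only, needs no new data and leaves the primary analysis as it is. The cost is that the check may have to be reported as inconclusive. With an illustrative margin of 0.15 SD and 500 v. 500, the CI fits inside only if the estimate is within 0.15 − 0.132 = 0.018 SD of zero, which happens about 21% of the time when there is no shift. At 180 v. 180 it cannot fit, because the half-width is 0.22 SD.

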## 9.2 Secondary Outcomes – Effectiveness

### Healthcare Utilization

Healthcare utilization metrics include the numbers of ER/urgent care visits, hospital admissions and days of stay, unscheduled visits, and supportive care visits for all three curative, non-curative and survivorship groups across the follow-up time frame for each individual. These data will be captured through the electronic medical record for within-NMHC utilization and by data collection directly from patients for outside-NMHC utilization at baseline, 6 and 12 months. Individual variables will be summarized across treatment groups using means and five-number summaries (minimum, 25th percentile, median, 75th percentile, maximum). For formal statistical analysis, we intend to create a global summary score of healthcare utilization by summing the counts of all variables listed above. Poisson regression will be used to compare the global healthcare utilization summary measures at 6- and 12-month time points across treatment arms in separate analyses for each time point. Primary analyses will compare Post-I EC v. Post-I UC as the primary predictor of interest with model adjustments for cluster, cancer continuum, gender, language preference, and time of enrollment. To evaluate potential contamination effects as described above, differences across the Post-I EC, Post-I UC and Pre-I groups will also be jointly evaluated. Overdispersion will also be evaluated, and if present, will be addressed through the use of quasi-Poisson modeling to account for additional variance.

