**Table 2 REDCap Study Assessment Frequency**

| Measure Assessment Battery                                                                                                                                                                                                                                                                                                   | 12-month Enrollment Period |   |   |   |   |   |   |   |   |   |    |    |    |
|------------------------------------------------------------------------------------------------------------------------------------------------------------------------------------------------------------------------------------------------------------------------------------------------------------------------------|----------------------------|---|---|---|---|---|---|---|---|---|----|----|----|
|                                                                                                                                                                                                                                                                                                                              | BL                         | 1 | 2 | 3 | 4 | 5 | 6 | 7 | 8 | 9 | 10 | 11 | 12 |
| REDCap Symptom Monitoring (PROMIS: Pain, Fatigue, Anxiety, Depression, & Physical Function; PRO-CTCAE; & Godin) [10-12 minutes]                                                                                                                                                                                              | x                          | x | x | x | x | x | x | x | x | x | x  | x  | x  |
| REDCap Comprehensive Assessment (Demographics (i.e., education, employment, insurance and captured only at baseline); CAHPS; PROMIS: Self-efficacy Managing Symptoms, Self- efficacy Managing Medication and Treatment, Informational, & Instrumental; CASE; FACT-G7; SILS; 1-item COST-FACIT; CollaboRATE) [25 -35 minutes] | x                          |   |   | x |   |   | x |   |   | x |    |    | x  |
| REDCap Resource Utilization [2-3 minutes]                                                                                                                                                                                                                                                                                    | x                          |   |   |   |   |   | x |   |   |   |    |    | x  |

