**Non-Consented Patients:**

A data use agreement established between Northwestern Medicine and Northwestern University was amended in July 2023 to facilitate the transfer of EDW data for this study's non-consented patient cohort in a way that complied with Illinois state privacy law. This amended data use agreement outlined safeguards and appropriate use of such data, including zip codes and sensitive protected health information. In August 2024, the Northwestern Medicine Privacy Steward advised the study team that a recent amendment to Illinois state privacy law has negated the need for the 2023 data use agreement, and that a HIPAA Waiver of Authorization will now cover the release of protected information, most significantly zip code and sensitive protected health information. Per IRB guidance, the study team has requested waivers of consent and HIPAA authorization for this study cohort.

In **Aim 2**, data will also collect *patient-reported health care service usage* using a selection of Resource Usage questions as part of the REDCap study assessment. These questions will assess the quantity of various health care services outside of the NM network (visits inside the NM network will be captured via EDW query), including the following services: physician visits (primary and specialty care, psychologists, psychiatrists); emergency department visits; inpatient hospital services. The health care usage questions will be administered in at baseline, 6 and 12 months. Additionally, *patient-reported health care satisfaction* will also be collected using Cancer CAHPS items at baseline, 3, 6, 9, and 12 months.

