## Secondary effectiveness outcomes in NU IMPACT:

- Healthcare utilization metrics ascertained via the electronic medical record for within-NMHC utilization and by data collection directly from patients for outside-NMHC utilization, collected at 6 and 12 months
  - Number of emergency room/urgent care visits
  - Number of hospital admissions
  - Hospital days of stay
  - Number of unscheduled visits
  - Number of supportive care visits
- Cancer treatment delivery metrics ascertained via the electronic medical record for within-NMHC utilization within 12 months of enrollment
  - Number of treatment breaks
  - Number of changes in regimen
- Cancer treatment delivery satisfaction, collected via survey at baseline and quarterly
  - CAHPS
  - Collaborate
- Health related quality of life, collected via survey at baseline and quarterly
  - FACT-G7
- Symptoms and toxicities, collected via survey at baseline and quarterly
  - PRO CTCAE
- Physical activity, collected via survey at baseline and monthly
  - GODIN
- Financial burden, collected via survey at baseline and quarterly
  - COST Facit V2
- Self-management metrics, collected via survey at baseline and quarterly
  - PROMIS Self Efficacy Manage Meds/Tx SF 4a v1.0
  - PROMIS Self Efficacy Manage Symptoms SF 8a v1.0
  - CASE
- Support and isolation metrics, collected via survey at baseline and quarterly (to be evaluated as potential mediators of treatment effects)
  - PROMIS Informational Support 2.0
  - PROMIS Instrumental Support 2.0
  - Social isolation

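### The healthcare utilisation model leaves out baseline utilisation: lost precision in a secondary outcome, not bias

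*Combined protocol and SAP*

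**What the plan says.** **Outcome and model.** In SAP 9.2, Healthcare Utilization, the outcome is a composite: "we intend to create a global summary score of healthcare utilization by summing the counts of all variables listed above". Its components are ER/urgent care visits, hospital admissions, days of stay, unscheduled visits and supportive care visits. The model is then specified: "Poisson regression will be used to compare the global healthcare utilization summary measures at 6- and 12-month time points across treatment arms", "with model adjustments for cluster, cancer continuum, gender, language preference, and time of enrollment". If overdispersion appears, quasi-Poisson is used. The same section also compares EC, UC and Pre-I jointly to look for contamination.

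**Baseline collection.** SAP 9.2 says patients report "outside-NMHC utilization at baseline, 6 and 12 months". Protocol 8.0 agrees: "The health care usage questions will be administered in at baseline, 6 and 12 months". Protocol Table 2 marks the resource utilisation row at baseline, month 6 and month 12. SAP 2.0, under secondary effectiveness outcomes, differs: "by data collection directly from patients for outside-NMHC utilization, collected at 6 and 12 months".

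**Comparator.** The PRO models in SAP 9.1, both the randomised comparison and the one extended to Pre-I, use the same adjustment factors plus the baseline PRO value.

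**The concern.** A baseline measurement is taken from patients, yet no section gives it a role in the utilisation analysis. The PRO analyses in the same SAP do use their baseline values, and no reason is given for the difference.

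The score adds hospital days to visit counts across curative, non-curative and survivorship patients, so patients are likely to differ widely in their underlying rate of use. If past use predicts later use, leaving it out widens the interval for the EC v. UC rate ratio and leaves chance imbalance in a skewed count uncorrected.

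The Pre-I comparison raises a further issue. Pre-I patients are not randomised and enrol in an earlier phase, so a difference in prior use could be mistaken for contamination or an implementation effect. The matching PRO analysis guards against this with the baseline value; the utilisation analysis does not.

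**Working it through.** **1. The plan's own figures.** The documents give no power, event rate or variance for utilisation. The only sample size calculation (SAP 6.0) concerns the PROs, and it reproduces. With 12 follow-ups and correlation 0.5, the variance factor is (1 + 11 × 0.5)/12 = 0.5417. Then 2 × 0.5417 × ((2.576 + 1.282)/0.3)² ≈ 179.1, taken as 180 per arm or 360 in total, and 360/(1 − 0.64) = 1,000. This point leaves those figures untouched.

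**2. Collection schedule.**

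| Place | Patient-reported use collected at |
|---|---|
| Protocol Table 2 | baseline, 6, 12 months |
| Protocol 8.0 text | baseline, 6, 12 months |
| SAP 9.2 | baseline, 6, 12 months |
| SAP 2.0 | 6, 12 months |

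**3. Size of the gain.** With covariate adjustment the residual variance is multiplied by about 1 − r², where r is the baseline-to-follow-up correlation remaining after the other covariates. The value of r is an assumption.

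| r | Variance factor 1 − r² | Reduction in SE, 1 − √(1 − r²) | 1,000 patients act like 1,000/(1 − r²) |
|---|---|---|---|
| 0.2 | 0.96 | 2.0% | 1,042 |
| 0.3 | 0.91 | 4.6% | 1,099 |
| 0.5 | 0.75 | 13.4% | 1,333 |

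**4. Check of the rule on counts.** A quasi-Poisson simulation used 1,000 patients allocated 1:1, 400 replicates per scenario, log-normal differences between patients, means of 3 or 6, a rate ratio of 0.85, and log(1 + baseline count) as covariate. All of these except the allocation and the 1,000 are assumptions.

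| Simulated r | r² | Observed cut in variance |
|---|---|---|
| 0.285 | 8.1% | 4.1% |
| 0.318 | 10.1% | 11.7% |
| 0.489 | 23.9% | 19.3% |
| 0.592 | 35.0% | 31.8% |
| 0.640 | 41.0% | 41.6% |
| 0 (no heterogeneity) | 0% | none (variance ratio 1.001) |

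The rule is about right, if sometimes a little generous. Without heterogeneity between patients there is neither gain nor loss.

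**5. Effect of the strata.** That simulation had no stratification factors, so its r is marginal. A further simulation (1,000 patients, means 2 and 4, assumed rate ratios between continuum groups, 300 replicates) shows what continuum absorbs. At a marginal correlation of 0.24 the cut fell from 9% to 4% once continuum was in the model. At 0.28 it fell from 5% to 2%.

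**6. A side effect.** In step 4 the adjusted quasi-Poisson standard error was too small in the most dispersed scenarios. It averaged 0.064 against an actual spread of 0.073 in one, and 0.055 against 0.068 in another. Quasi-Poisson takes the variance as proportional to the mean, whereas here it rises faster. A robust (sandwich) standard error does not rely on that assumption.

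**The case against.** The strongest reply is that nothing is wrong with the planned comparison. Allocation is 1:1 and stratified by cluster, continuum, gender and language. The model adjusts for all four plus time of enrolment, and overdispersion is provided for. That stands: a reader might infer that the EC v. UC estimate is biased or invalid, and randomisation rules that out.

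The second reply is that the precision is not simply waiting to be used. This also stands. Protocol 8.0 limits the baseline questions to services outside the NM network (physician visits, emergency visits, inpatient services), while the score covers use inside and outside NMHC with a different set of components. A matching baseline needs pre-consent EHR counts. Protocol 8.0 dates encounters in days from consent, so these look obtainable, but no look-back window is defined for either source.

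Third, r is unknown and may be low. Protocol 3.0 requires curative-intent patients to have started primary treatment within the past 3 months, so their prior use may belong to a different phase of care. The strata already absorb part of the variation between patients. This limits the size of the gain but does not remove the reason to adjust.

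Fourth, the time points in SAP 2.0 can be read as outcome times only. A reader might infer that the model omits baseline because it follows that shorter list. The documents do not support this: SAP 9.2, which contains the model, lists baseline itself. Neighbouring survey items in SAP 2.0 do name baseline, so the wording still needs reconciling.

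**Conclusion.** The point holds as a modest recommendation on a secondary outcome. The utilisation models have no baseline term although baseline resource use is collected and the PRO models adjust for baseline. For EC v. UC the consequence is lost precision and uncorrected chance imbalance; for the Pre-I comparison, possible confounding as well.

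The size cannot be fixed from the documents. It rests on the assumed r after the stratification factors and on overdispersion, which the SAP provides for but has not yet observed. Over r = 0.2 to 0.5 the variance cut is about 4% to 25%. A reader might take the top of that range as the expected gain, but nothing in the documents favours it over the bottom. A reader might also extend the point to every Poisson model in SAP 9.2. It does not extend to treatment breaks and regimen changes, for which prior utilisation is not the baseline value.

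**What to change.** 1. In SAP 9.2, Healthcare Utilization, prespecify log(1 + baseline utilisation) as a covariate in the 6- and 12-month models, before any comparison by arm is seen. State that it does not carry over to the treatment-break and regimen-change models that borrow the same approach.
2. Define the covariate as the EHR count of the same score components in a fixed pre-consent look-back window, plus the baseline survey count of outside-NMHC use over its stated recall period. Give both periods.
3. For missing baseline survey values, use a missing-value indicator in the randomised comparison. In the Pre-I comparison, where an indicator can bias, use the multiple imputation already named in SAP 9.1.
4. Report robust standard errors for the adjusted rate ratio, given step 6 of the working.
5. Reconcile the schedule in SAP 2.0 with SAP 9.2, Protocol 8.0 and Table 2. This is a wording correction.

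The cost is one extra EHR derivation with a defined window, and a few lines of SAP text. SAP 1.0 says SAP changes need no protocol amendment. No new patient questions are needed. The downside is that the effort may buy little if r is near 0.2.
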